#### 5.5.3 Outcome of AEs

The outcomes of ARs/AEs include: (1) Recovery; (2) Not yet recovered; (3) Recovered but sequelae; (4) Death; (5) Loss of visit.

#### 5.5.4 Relationship between AE and vaccination

Investigators should make the best interpretation of AE, and assess the possible causal relationship between vaccination and reactions (such as history of underlying diseases, combined treatment of causation). This applies to all AEs, including severe ones and non-severe ones. The assessment of causality will be reasonably explained in the following or more aspects of the event: The similar reaction to the solution was observed in the past; identical events of similar types solution have been reported in the literature; the incident occurred along with the time of the vaccination, and again after the secondary vaccination According to definitions, all the solicited AE (that is, the local adverse event of the collection of the report) will be considered to be related to vaccination. The causal relationship of AE should be evaluated according to the following questions, and according to your judgment, the reasonable possibility of relationship between AE and vaccination is caused by the vaccination:

1. Related: there is a suspicion that a link between vaccine and the AE (do not need to be determined);

the vaccine has a reasonable potential for promoting the AE.

2. Unrelated: there is no suspicion that a link exists between vaccine and the AE; there are other more likely causes, and vaccination has not been suspected to promote the AE.

#### **5.5.5 Treatment of AEs/ARs**

An adverse event (AE) is any untoward medical occurrence in a patient or clinical trial participant administered with a pharmaceutical product and which does not necessarily have a causal relationship with this treatment.

Adverse reactions (AR): unexpected or harmful reactions in the process of vaccination according to the prescribed dose and procedure, usually related to vaccination.

Serious adverse event (SAE): refers to the following important medical events, whether or not related to the vaccine clinical trial, including: 1) death; 2) life threatening; 3) hospitalization or prolonged hospitalization; 4) permanent or significant disability / loss of function; 5) congenital abnormality or birth defect; 6) severe adverse event It may lead to other important medical events, such as those listed above without treatment.

Suspected Unexpected Serious Adverse Reaction (SUSAR): Suspected adverse reactions refer to the adverse reactions of subjects at any dose that have nothing to do with the purpose of the medication. After analysis, it is considered that the relationship with the drug is at least likely to be related; Unexpected refers to adverse reactions. The nature, extent, consequences, or frequency are different from the expected risks described in the previous plan or other related materials (such as the investigator's manual and instructions).

If subjects have any clinically significant disease/event after vaccination, it should be reported to the investigators as soon as possible. The investigators should follow up the adverse reaction/event until the symptoms disappear or the symptoms stabilize. When the investigators deem it necessary, treatment will be provided unconditionally to relieve the pain caused by the adverse reaction/event for the subjects. All medical treatments will be recorded at each follow-up.

In the event of a serious adverse event/reaction, the investigators should take necessary measures quickly, fill in the "Serious Adverse Event Report Form" within 24 hours, and report it to the principal investigator in the form of fax or E-mail.

### **5.5.6 Treatment of pregnancy events**

Vaccination of the trial is not allowed during pregnancy. Before vaccination, the subjects will be given urine pregnancy test, and those who are positive in the urine pregnancy test should not be included in the group. If a pregnancy event occurs within 6 months of the visit, the Pregnancy Case Survey Form needs to be filled out.

## **5.6 Immunogenicity evaluation**

### **5.6.1 Samples collection**

"0-28 days" immunization regimen:

At V0 (day 28 after the prime dose and before the booster dose) and V3 (day 28 after the booster dose), 20 ml of venous blood will be collected by vacuum anticoagulant blood collection vessel. PBMC and serum will be separated to detect the antibody level, immune cell differentiation and antibody spectrum induced by the vaccine.

In V2 (day 14 after the booster dose) and V4 (month 6 after the booster dose), 10ml of venous blood will be collected by vacuum anticoagulant blood collection vessel, and the serum will be separated to detect the antibody level, immune cell differentiation and antibody spectrum induced by the vaccine.

"0-56 days" immunization regimen:

At V-1 (day 28 after the prime dose) and V3 (day 28 after the booster dose), 20 ml of venous blood will be collected by vacuum anticoagulant blood collection vessel. PBMC and serum will be separated to detect the antibody level, immune cell differentiation and antibody spectrum induced by the vaccine.

At V0 (day 56 after the prime dose and the booster dose), V2 (day 14 after the booster dose) and V4 (month 6 after the booster dose), 10ml of venous blood will be collected by vacuum anticoagulant blood collection vessel, and the serum will be separated to detect the antibody level, immune cell differentiation and antibody spectrum induced by the vaccine.

The serum samples of this clinical trial will be used to evaluate the immune response level of the research vaccine. For other studies, the approval of the ethics committee and the consent of the subjects are required.

## **5.6.2 Preservation and transportation of samples**

Unified operation standards are adopted in the process of preservation and transportation. The storage temperature of serum should be - 20°C and below, and it should be transported to the testing laboratory in time. The separation, transportation and preservation of BPMC used for the differentiation of immune cell population and the detection of antibody spectrum are operated by the third party laboratory according to the standard operating procedures.

## **5.7 Data management**

### **5.7.1 Data collection, entry and reporting**

Vaccination and visit records and other original data should be clearly recorded, which should be filled in with a black signature pen. The errors of the original records should not be wiped or covered, but should be crossed off, put the corrected data aside, and signed and dated by the investigators.

Fill in all the case report forms according to the protocol. Case report form is used to record the data of clinical trials. It is an important part of clinical trials and research reports. It should be filled in clearly and completely. It is required to fill in with a black signature pen. The mistakes should not be erased or covered by the original record. Instead, a horizontal line should be drawn on it, and the corrected data should be indicated in the blank beside it. The revised researcher should sign his name and indicate the date.

According to the requirements of the scheme, data collection, biological sample collection and examination should be carried out in each visit time window, and the original documents and records should be complete, and the examination conclusions should be entered into the case report form (CRF) in time.

### **5.7.2 Verification of data records**

The quality controller should check the data record regularly and irregularly until the CRF is completed. Before withdrawing the CRF, the quality controller should carefully check the CRF number of the subjects, the number of pages of each CRF and the necessary signature of the researcher. The main content of quality control should focus on the following links: signing of informed consent, volunteer

screening, immunization, management of experimental vaccine, safety observation, collection and preservation of immunogenic samples, etc. the consistency of research data and original data should be focused on, and manual verification should be carried out. The verification results shall be recorded. The transfer of CRF and other research materials should be documented.

### **5.7.3 Database establishment and data entry**

#### Establishment of database:

The personnel in charge of data management shall establish the database structure and check procedures according to CRF, ensure that the database can be correctly converted to SAS file format, and modify and confirm the database structure through trial input.

#### Further verification of CRF:

Before entering CRF, data management personnel should check CRF again, mainly to see if there are omissions and obvious errors.

#### Data entry:

After the training of data entry personnel, data entry is carried out by two persons and two computers.

#### Data comparison and examination:

Check the consistency of the database data independently completed by the two people, report the inconsistent values and information, and then check the original data item by item to correct until the two databases are consistent. Use the computer program that has been written and confirmed to logically check the data, issue the query form and ask the researcher to confirm and then modify the database until there is no doubt. It is necessary to select a certain number of CRF randomly according to a certain proportion to control the quality of the database, and compare with the data in the database manually, so as to ensure that the data in the database is consistent with the CRF content.

### **5.7.4 Database locking**

Before statistical analysis, it is necessary to conduct a check and clean of the database. The analyzed population will be set according to the definition of the data sets, including the FAS set, PPS set and safety analysis data set, and to determine the deviation from the regimen and its impact on the analysis data set. After the database is cleaned, the database will be locked, and the statistical analysis plan is locked at the same time.

## **5.8 Statistics Plan and Statistical Analysis**

### **5.8.1 Statistical plan**

The statistical analysis of this study will be completed in two stages. After the subjects complete the visit 28 days after the booster dose immunization, the study database will be recorded, reviewed and locked for the first stage statistical analysis.

The safety and immunogenicity data after 28 days till 6 months after immunization will be collected, reviewed and locked for the second stage statistical analysis and summary.

### **5.8.2 Selection of analysis data sets**

Safety data set (SS):

The safety evaluation should be conducted for all participants who receive vaccines after randomization. Data violating the protocol should not be eliminated.

Immunogenicity data set:

Full Analysis Set (FAS): It is defined as ideal participant population determined according to the ITT (Intention-to-treat analysis) principle, all participants who meet the inclusion / exclusion criteria, and are randomized and given vaccine and have at least one post-immunization blood test results are included in the FAS.

Per-Protocol Set (PPS): It is a subset of FAS. Participants in this set are more compliant with the protocol, experience no major protocol violation, comply with all inclusion criteria / exclusion criteria, and complete the vaccination within the time window as required in the protocol and all blood samplings are included in the PPS set. Participants who violate the trial protocol, such as poor compliance or lost to follow-up, and those who suffer intercurrent SARS-CoV-2 infection will not be included in this analysis set.

In this trial, the FAS will be used as the primary analysis set. However, PPS should be analyzed simultaneously. Any inconsistency between PPS and FAS analysis results should be discussed in the report.

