### **5.8.3 Data statistics method**

During statistical analysis, first, the number of completed cases and drop-out cases should be checked. Then demographic and baseline characteristics of each group at enrollment should be analyzed to investigate intergroup comparability. Efficacy evaluation of vaccine includes the determination of evaluation indicators and intergroup comparison of efficacy. Safety evaluation includes the statistics of clinical ARs/AEs.

Participant elimination criteria: participants don't meet the inclusion criteria; data and information after vaccination are not followed up; information and data after randomization are seriously missing; participants meet exclusion criteria but are not withdrawn; participants receive wrong vaccination or

incorrect dose.

Safety analysis in this trial mainly includes descriptive analysis of the incidence of ARs/AEs.  $\chi^2$  test may be carried out for intergroup comparison, and Fisher's exact test may be performed if necessary. After immunization, the number of case-times and person-times of local AEs in the high-dose group will be calculated (with conventional calculation method). The number of person-times will be calculated based on the highest severity in both arms, and the number of case-times will be calculated based on the cumulative local AEs actually occurring at the vaccination site. Logarithmic transformation is required for analysis of immunogenicity indicator of antibody level which should be expressed as GMT, standard deviation, median, maximum and minimum and 95% confidence interval. Classification indicators will be compared between groups. Antibody seroconversion rate will be analyzed by  $\chi^2$  test and Fisher's exact test may be used if necessary. Study data at different time points will be analyzed with statistical analysis for repeated measurement data.

SAS 9.4 is adopted for all statistical analyses with two-sided test. The P value is directly calculated while carrying out Fisher's exact test when test statistics and corresponding P values are given, and in case of  $P \leq 0.05$ , the difference is statistically significant.

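### The primary analysis set is labelled intention-to-treat but requires eligibility, the elimination list names no analysis set, and the per-protocol set requires every blood draw

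*Protocol*

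**What the plan says.** All references are to the protocol.

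- **Safety set (5.8.2).** Everyone vaccinated after randomization is evaluated, and "Data violating the protocol should not be eliminated".
- **FAS (5.8.2).** "It is defined as ideal participant population determined according to the ITT (Intention-to-treat analysis) principle". Membership is then given to "all participants who meet the inclusion / exclusion criteria, and are randomized and given vaccine and have at least one post-immunization blood test results". The section states that "the FAS will be used as the primary analysis set", with the PPS analysed alongside and any inconsistency discussed.
- **PPS (5.8.2).** Besides eligibility and no major violation, participants who "complete the vaccination within the time window as required in the protocol and all blood samplings are included in the PPS set". No timepoint limits the sampling condition.
- **Elimination list (5.8.3).** "Participant elimination criteria: participants don't meet the inclusion criteria". It continues with absent follow-up after vaccination, then "information and data after randomization are seriously missing; participants meet exclusion criteria but are not withdrawn; participants receive wrong vaccination or" an incorrect dose. No analysis set is named and no threshold for serious missingness is given. The next paragraph is the safety analysis.
- **Local adverse events (5.8.3).** After vaccination, "the number of case-times and person-times of local AEs in the high-dose group will be calculated", with the person count taken at the highest severity in both arms.

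**The concern.** An intention-to-treat set should not depend on a later finding that someone was ineligible, and still less on receipt of the wrong vaccine or on the completeness of follow-up. Those last two arise after randomization. Removing participants for them can separate the groups on factors related to outcome, in the set that carries the primary neutralizing-antibody comparison.

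The list also covers people whom the safety rule says to keep. Section 4.6.1 classes ineligible enrolment and incorrect intervention as protocol violations. Section 5.8.2 keeps violating data in the safety set, while the unscoped list in 5.8.3 eliminates those same participants. Two programmers could build different sets from this text and both claim to follow it.

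The PPS condition makes membership at day 14 or day 28 depend on draws taken months later. The protocol treats a missed draw mildly elsewhere: section 4.6.2 calls it a deviation, and section 4.4 lets participants refuse blood draws alone and stay in the study.

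**Working it through.** **1. Which rule removes whom**

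| Reason | FAS definition, 5.8.2 | Elimination list, 5.8.3 (no set named) | Safety-set rule, 5.8.2 |
|---|---|---|---|
| Ineligible | removed | removed | kept |
| Wrong vaccine or dose | not mentioned | removed | kept |
| Seriously missing data | removed only if there is no post-immunization result | removed | kept if vaccinated |

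The FAS is an immunogenicity set, so its definition does not itself clash with the safety rule. The clash comes from the list. Eligibility is fixed before randomization; wrong vaccine and missing data are not.

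**2. PPS membership against the schedule**

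The protocol abstract gives five draws for the 0-28 regimen (V0, V2, V3, V6, V8) and six for the 0-56 regimen (V-1 added). V8 is month 6 after the second booster. In Tables 1 and 2 it falls 330 − 28 = 302 days and 360 − 56 = 304 days after the first booster, about 10 months.

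Section 5.8.1 locks the first-stage database after the day-28 visit, and section 5.7.4 sets the populations before the lock. If the booster in 5.8.1 is the first, V6 and V8 are outstanding at that lock. If it is the second, V8 is. Read literally, PPS membership cannot then be settled.

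Section 5.6.1 still describes a schedule whose last draw is at V4, month 6 after the booster. It must be reconciled with the tables, which show no draw at V4.

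**3. The plan's sample size, reproduced**

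Inputs from section 3.4: 1:60 against 1:20, so δ = log10(3) = 0.477; SD 0.6 on the log10 scale; 2:1 allocation; 80% power. Section 5.8.3 gives the two-sided test at 0.05.

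Normal approximation: n(control) = (1.960 + 0.842)² × 0.6² × (1 + 1/2) / 0.477² = 18.6, so 19 and 38. By the noncentral t distribution, 38/19 gives 79.4% and 40/20 gives 81.5%. The stated 40 and 20 per regimen are reproduced. Section 3.4 states no allowance for loss, so losing two vaccine and one control participant already takes power just under 80%.

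**4. Size of one elimination**

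1/20 = 5% of a regimen's control arm; 1/40 = 2.5% of its vaccine arm.

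**5. Size of the all-draws rule, PPS only**

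Assumption: each draw is missed independently with probability m. The protocol gives no rate, so m = 3% and 5% are illustrations. The share kept over k draws is (1 − m)^k. Power is the noncentral t at 40 and 20 times that share.

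| Draws required | Kept, m = 3% | Kept, m = 5% | Power, m = 3% | Power, m = 5% |
|---|---|---|---|---|
| 3 (V0, V2, V3; 0-28 regimen to day 28) | 0.97³ = 91% | 0.95³ = 86% | 78% | 75% |
| 5 (0-28 regimen, all) | 0.97⁵ = 86% | 0.95⁵ = 77% | 75% | 70% |
| 6 (0-56 regimen, all) | 0.97⁶ = 83% | 0.95⁶ = 74% | 74% | 68% |

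A visit-specific rule needing only the baseline sample and that visit's sample would keep 0.97² = 94% to 0.95² = 90%.

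**6. Local adverse events**

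Sections 3.1 and 3.4 give ZF2001 and influenza vaccine groups within each regimen and no dose levels. A high-dose group does not exist. Both arms may mean limbs or treatment arms; a count in a high-dose group fits neither.

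**The case against.** Several arguments limit the point.

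- **The elimination list.** A reader might infer that wrong-vaccine recipients will be dropped from safety and their exposure hidden. The documents do not establish that. The list names no set, 5.8.2 has a specific rule for the safety set, and 5.7.4 says populations follow the set definitions. What stands is that the scope is unstated and that, taken literally, the two sections conflict.
- **Eligibility.** It is a pre-randomization characteristic, screened under 5.3. Populations are set before lock, and under 3.5.3 blinding is lifted only with the initial day-28 analysis. Bias from eligibility exclusions is therefore likely small at the first stage. That is less assured at the second stage, when only subjects and safety observers remain blinded, and it does not cover the post-randomization criteria.
- **The safety endpoint.** A reader might infer that the high-dose wording prevents reporting of the primary solicited adverse event endpoint by group. It does not: 5.8.3 separately provides incidence with chi-square or Fisher tests between groups. The sentence is inapplicable, not disabling.
- **The PPS.** All blood samplings could mean the samples due at each analysis stage, and visit flags are often left to the statistical analysis plan. That reading is sensible, but the sentence as written does not say it.
- **The power figures.** They concern the PPS, not the primary FAS. Under the 5.8.2 definition, a missed V8 removes nobody from the FAS who has another post-booster result. Missed draws usually cluster in participants who leave, so the independence formula overstates the loss. Section 3.4 also powers day 28, not day 14. All of this stands.

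**Conclusion.** The point holds as a defect of wording that changes who is analysed. The primary set is described as intention-to-treat and defined otherwise. An unscoped list adds removals that are partly post-randomization and conflict with the safety-set rule if read literally. The PPS sampling condition, on the current schedule, discards valid earlier results and cannot be settled at the first-stage lock. The high-dose sentence does not apply to this trial.

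The size for the FAS is 5% of a regimen's control arm per elimination there; the protocol gives no basis for predicting how many eliminations will occur. For the PPS, power falls from about 81% to about 75-70% with five draws and 74-68% with six, under assumed independent missed-draw rates of 3-5%. This is the upper end of the loss at those rates, and part of it would occur under any rule needing the draws to day 28. It should not be read as a loss of power in the primary analysis.

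**What to change.** Revise 5.8.2 and 5.8.3 as follows:

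1. **FAS:** all randomized and vaccinated participants with at least one post-booster result, analysed as randomized regardless of eligibility.
2. **Elimination list:** state that it applies to the PPS only, and either define seriously missing or drop the phrase in favour of the visit-specific rule in item 4.
3. **Safety set:** all vaccinated participants, by vaccine received, with no eliminations.
4. **PPS:** define it by visit, requiring the doses due by then within window, the baseline sample and that visit's sample. Reconcile the draws listed in 5.6.1 with the visit tables.
5. **Local adverse events:** replace the high-dose group and both-arms wording with counts in each randomized group after each booster.

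The cost is an amendment to two sections, matching text in the statistical analysis plan, and visit-specific PPS flags in the analysis data. No extra participants, visits or samples are needed.

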### **5.8.3 Data statistics method**

During statistical analysis, first, the number of completed cases and drop-out cases should be checked. Then demographic and baseline characteristics of each group at enrollment should be analyzed to investigate intergroup comparability. Efficacy evaluation of vaccine includes the determination of evaluation indicators and intergroup comparison of efficacy. Safety evaluation includes the statistics of clinical ARs/AEs.

Participant elimination criteria: participants don't meet the inclusion criteria; data and information after vaccination are not followed up; information and data after randomization are seriously missing; participants meet exclusion criteria but are not withdrawn; participants receive wrong vaccination or

incorrect dose.

Safety analysis in this trial mainly includes descriptive analysis of the incidence of ARs/AEs.  $\chi^2$  test may be carried out for intergroup comparison, and Fisher's exact test may be performed if necessary. After immunization, the number of case-times and person-times of local AEs in the high-dose group will be calculated (with conventional calculation method). The number of person-times will be calculated based on the highest severity in both arms, and the number of case-times will be calculated based on the cumulative local AEs actually occurring at the vaccination site. Logarithmic transformation is required for analysis of immunogenicity indicator of antibody level which should be expressed as GMT, standard deviation, median, maximum and minimum and 95% confidence interval. Classification indicators will be compared between groups. Antibody seroconversion rate will be analyzed by  $\chi^2$  test and Fisher's exact test may be used if necessary. Study data at different time points will be analyzed with statistical analysis for repeated measurement data.

SAS 9.4 is adopted for all statistical analyses with two-sided test. The P value is directly calculated while carrying out Fisher's exact test when test statistics and corresponding P values are given, and in case of  $P \leq 0.05$ , the difference is statistically significant.

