|--------------|---------------------------------------------------------------------------------------------------------------------------------------------------------------------------------------------------------------------------------------------------------------------------------------------------------------------------------------------------------------------------------------------------------------------------------------------------------------------------------------------------------------------------------------------------------------------------------------------------------------------------------------------------------------------------------------------------------------------------------------------------------------------------------------------------------------------------------------------------------------------------------------------|
|              | 
at 2 ~ 8°C.
 
“Placebo”: trivalent split influenza vaccine
 
Manufacturer: Dalian Aleph Biomedical Co., Ltd.
 
Specification: 0.5ml/bottle, be stored and transported at 2 ~ 8°C.
 
Immunization:
 
Intramuscular injection at the lateral deltoid muscle of the left upper arm.
 
0-28 days regimen: The prime dose of Ad5 vectored vaccine against COVID-19, followed by protein subunit vaccine or commercial influenza vaccine 28 days apart.
 
0-56 days regimen: The prime dose of Ad5 vectored vaccine against COVID-19, followed by protein subunit vaccine after 56 days apart.
 
For 0-28 days regimen and 0-56 days regimen, all participants receive a boost vaccination with ZF2001 at 4 months after the 1st boost dose.
                                                                                                       |

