### **3. Trial Design**

#### **3.1 Design procedures**

This study is a single center, randomized, observer blind, placebo-controlled heterologous prime-boost immunization clinical trial, with “0-28 days” and “0-56 days” immunization regimens. The subjects are divided into two age groups, i.e. 18-59 years and 60 years and above.

Stage 1: According to the "0-28 days" regimen, sixty eligible subjects (30 in each age group) meeting the protocol requirements will be randomly assigned in a 2:1 ratio to receive a RBD-based protein subunit vaccine (CHO) or placebo (influenza vaccine).

Stage 2: According to the "0-56 days" regimen, sixty eligible subjects (30 in each age group) meeting the protocol requirements will be randomly assigned in a 2:1 ratio to receive a RBD-based protein subunit vaccine (CHO) or placebo (influenza vaccine).

Stage 3: For 0-28 days regimen and 0-56 days regimen, all participants receive a boost vaccination with ZF2001 at 4 months after the 1st boost dose.

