##### **3.2.2 Secondary endpoints:**

###### **1. Safety endpoints**

- Incidence of adverse reactions within 28 days after each booster dose;
- Incidence of unsolicited AE within 28 days after each booster dose;
- Incidence of serious adverse events(SAE) from the 1st booster dose to the month 6 after the 2nd booster vaccination

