### 3.4 Sample size calculation

Sample size:

Hypothesis: GMT of vaccine group is superior to that in the control group at day 28 after the booster vaccination.

The baseline GMT level before the booster immunization is expected to be about 1:20 ( $\log_{10}X=1.3$ ) after one dose of prime vaccination with Ad5 vectored COVID-19 vaccine. After the booster dose, GMT level in the vaccine group is estimated to reach 1:60 ( $\log_{10}X=1.78$ ), while the control group remains 1:20. Assume that the Standard Deviation is about 4 ( $\log_{10}X=0.6$ ), and the allocation ratio for the vaccine group and placebo group is 2:1, then the minimal sample size to provide 80% power calculated is 40 and 20, respectively.

In each regimen group, subjects are stratified to two sub-age groups: 18-59 years and 60 years or above.

Table 3. Sample size of each immunization regimen

| regimen   | Sub-age group     | sample size                |                       |
|-----------|-------------------|----------------------------|-----------------------|
|           |                   | Experimental vaccine group | Placebo control group |
| 0-28 days | 18-59 years       | 20                         | 10                    |
|           | 60 years or above | 20                         | 10                    |
| 0-56 days | 18-59 ages        | 20                         | 10                    |
|           | 60 years or above | 20                         | 10                    |
| Total     | —                 | 80                         | 40                    |

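### Section 5.8.3 counts local reactions in a high-dose group the trial does not have, and the single SAE window spans the controls' own ZF2001 dose

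*Protocol*

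**What the plan says.** **Local reactions.** Section 5.8.3, after describing the incidence of adverse reactions and events, adds: "After immunization, the number of case-times and person-times of local AEs in the high-dose group will be calculated (with conventional calculation method". It goes on: "The number of person-times will be calculated based on the highest severity in both arms". Case-times are to be the cumulative local events at the vaccination site.

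**Groups in the trial.** Section 3.1 has eligible subjects in each regimen who "will be randomly assigned in a 2:1 ratio to receive a RBD-based protein subunit vaccine (CHO) or placebo (influenza vaccine". Table 3 in section 3.4 has two columns, "Experimental vaccine group" (80 in total) and a placebo control group (40). Section 5.4.1 lists one ZF2001 strength (25 µg in 0.5 ml) and one influenza vaccine.

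**Injection.** The abstract specifies: "Intramuscular injection at the lateral deltoid muscle of the left upper arm". Section 5.4.2 gives the left arm priority rather than requiring it.

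**SAE endpoint.** Section 3.2.2 and the abstract define one SAE incidence, from the first "booster dose to the month 6 after the" second booster. Stage 3 in section 3.1 says that "all participants receive a boost vaccination with ZF2001 at 4 months after the 1st boost dose", controls included.

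**Grouping rule.** Neither the safety set in section 5.8.2 nor the methods in section 5.8.3 says how SAEs after V4 are grouped for participants first given influenza vaccine.

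**The concern.** The instruction to count local reactions points to a group with no members, and the rule for the count does not say whose severity is maximised over what. A programmer would have to guess, and two could produce different tables.

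The SAE endpoint covers a period in which the control group changes product. Before V4 a comparison by randomised arm is ZF2001 against influenza vaccine. After V4 both arms have had ZF2001 and differ only in whether it is the first or the second ZF2001 dose. One cumulative table by randomised arm would mix these two comparisons under a placebo label, and a reader would probably take it as the long-term ZF2001-versus-control comparison.

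**Working it through.** **Part A: the local-reaction count.** No arithmetic applies, so the texts are set side by side.

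- Sections 3.1, 3.4 and 5.4.1 give two products per regimen and one ZF2001 strength. Nothing maps high-dose to either product.
- Read as treatment arms, the phrase both arms conflicts with the preceding sentence, which confines the count to one group. It also gives no maximum to take for a person, since each participant is in only one treatment arm.
- Read as limbs, it does not fit one injection per vaccination visit. Because 5.4.2 only prefers the left arm, a participant might have used both limbs over two boosters. A maximum across limbs would then merge two boosters, whereas the endpoints are per booster.

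The count therefore lacks a defined group, and the person-time rule lacks a defined unit. Incidence of reactions and events is planned separately in the same section and does not depend on it.

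**Part B: the SAE window.** Inputs are the scheduled days in Tables 1 and 2.

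| Regimen | V0 (1st booster) | V4 (2nd booster) | V8 (last visit) |
|---|---|---|---|
| 0-28 | Day 28 | Day 150 | Day 330 |
| 0-56 | Day 56 | Day 180 | Day 360 |

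The protocol has no calculated figure on this point. Its stated intervals are reproduced first:

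- V4 − V0 = 150 − 28 = 122 and 180 − 56 = 124 days, about 4 months.
- V8 − V4 = 330 − 150 = 180 and 360 − 180 = 180 days, 6 months.

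Share of the control arm's window after its own ZF2001 dose = (V8 − V4)/(V8 − V0):

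- 0-28: 180/302 = 59.6%
- 0-56: 180/304 = 59.2%

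**Illustration of the pull towards the null.** The protocol gives no SAE rates, so the following are assumptions: a constant SAE rate on each product, with ZF2001 multiplying it by R from the first ZF2001 dose onward. The rate ratio by randomised arm is then R × (V8 − V0)/[(V4 − V0) + R × (V8 − V4)].

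- R = 2, 0-28: 2 × 302/(122 + 2 × 180) = 604/482 = 1.25
- R = 2, 0-56: 2 × 304/(124 + 2 × 180) = 608/484 = 1.26
- As R grows without limit, the ratio tends to 302/180 = 1.68 or 304/180 = 1.69.

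The same idea on cumulative risks, assuming a control rate a = 0.005 per 30 days and writing m0 and m1 for the periods before and after V4 in 30-day units (0-28: m0 = 122/30, m1 = 6):

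- ZF2001 arm: 1 − exp[−aR(m0 + m1)]
- Control arm: 1 − exp[−a·m0 − aR·m1]

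| R | Risk ratio over whole window, 0-28 | Risk ratio before V4, 0-28 |
|---|---|---|
| 1.5 | 1.15 | 1.49 |
| 2 | 0.0958/0.0772 = 1.24 | 1.98 |
| 3 | 1.34 | 2.94 |
| 5 | 1.42 | 4.80 |

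The 0-56 regimen gives whole-window ratios of 1.15, 1.24, 1.35 and 1.43.

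**The case against.** The strongest case is that the protocol misassigns nothing. It does not say that SAEs after V4 will be listed under the randomised arm. Grouping by product and period is commonly settled in a statistical analysis plan, which may exist. The SAE endpoint is an incidence, the safety analysis is mainly descriptive with optional tests, and an incidence over all follow-up is a legitimate summary. On local reactions, the sentence concerns an additional count, and changing one label would nearly restore it.

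Much of this stands. A reader might infer that safety results are being put into the wrong groups, or that the primary safety endpoint is compromised. The document supports neither. The high-dose wording leaves a count undefined; it does not move events between groups. Solicited events (7 days), adverse reactions and unsolicited events (28 days) are all defined per booster, so the window that spans V4 does not mix them. The ratios above are illustrations, and no dilution of a planned test can be claimed.

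What does not fall to the objection is that the high-dose group is a wrong statement in the protocol, not a detail left for later. The SAE window is likewise fixed in the endpoint definition, and that definition has no division at V4.

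**Conclusion.** The point holds in a limited form.

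- The count of local case-times and person-times in 5.8.3 cannot be carried out as written, because its group does not exist and its severity rule is ambiguous. The consequence is confined to a descriptive table.
- About 60% of the control arm's SAE window follows its own ZF2001 dose. This rests only on the scheduled visit days and ignores visit windows. A cumulative table by randomised arm, if one is made, would not compare ZF2001 with control. The pull towards the null assumes that ZF2001 acts in the same direction in controls after V4 as in the ZF2001 arm before it. Its size is unknown.

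With 40 controls, SAEs will probably be few. The likely harm is a mislabelled or uninterpretable table rather than a lost confirmatory result. Both corrections should be made, and neither calls the primary analyses into question.

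**What to change.** 1. In section 5.8.3, replace the reference to the high-dose group with: *in each group by vaccine received at that booster (ZF2001 or influenza vaccine), by regimen and booster number*.
2. For person-times only, replace the both-arms rule with: *each participant's highest severity after that booster*. Leave case-times as cumulative local events.
3. Keep the overall SAE incidence, and add two windows: first booster to V4, as randomised ZF2001 versus influenza vaccine; and V4 to V8, when all participants have had ZF2001, split by first or second ZF2001 dose, with no placebo label.

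The cost is a wording change, one more set of tables and fewer events per window. On the assumed control rate above, the expected number of controls with an SAE before V4 is 20 × [1 − exp(−0.005 × 122/30)] + 20 × [1 − exp(−0.005 × 124/30)] = 0.40 + 0.41, or about 0.8. The split tables should therefore be read descriptively. No new data are needed.
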